### Strengths and limitations

The study has several strengths. First, it is based on a strong conceptual framework, using the HAPA model to examine the social cognitive factors and processes involved in health behaviour change. Moreover, the study considers the realities and experiences of the study population to contextualise exercise behaviour, which enhances its ecological validity. Another strength of the study is its multidisciplinary and synergistic nature, involving experts from various fields including Health Psychologists, Clinical Psychologists, Exercise & Sport Psychologists, Gynaecologists and Sport & Exercise Physicians, which broadens the scope of the procedures and results. In addition, the focus on middle-aged women’s health and well-being contributes to both existing knowledge and its social applicability.

An important limitation of the study concerns the sample size. However, we believe that the chosen sample is justified for two reasons. First, it is necessary to include participants with three different levels of physical behaviour (non-active, initiators and regularly active). Second, the study involves an exhaustive exploration of the variables of interest in each evaluation phase, which will not be feasible with a larger sample as this would hinder the optimal monitoring of participants. In addition, as mentioned, the expected sample size per study subgroup exceeds the calculated sample size.

Further, it is worth noting that our study primarily relies on self-reported data. However, previous research has demonstrated the reliability, validity and accuracy of self-reports for gynaecological data [118], psychosocial data [119], behavioural data [120] and physical activity data [121, 122], while both objective and subjective methods have been shown to offer convergent yet complementary information. Given that single item measures generally perform more poorly than multi-item questionnaires [123], we prioritised the use of multi-item questionnaires in our assessment protocol.

In addition, there is a lack of previous research on the fit of the HAPA model for predicting active behaviour in early postmenopausal women [64, 65, 68]. In order to more thoroughly explore the influences of HAPA constructs on exercise behaviour adoption, longer interventions (i.e., exercise programme, HAPA-based intervention) and follow-ups would be necessary. Nevertheless, 3 to 4 months is considered to be sufficient to progress through the intention to action phases, while an additional 12-month period allows for the transition from initiation to the initial sustainability of habits, taking into account the natural fluctuations in behaviour [50, 124–128]. Evidence suggests that the main motivational and self-regulatory changes that improve adherence occur in the first 1–2 months of practice [129] and the first 6 to 12 months of adherence [130], respectively.

Finally, the type of methodology used in the design and data analysis (i.e., methodological and statistical control) will make it possible to overcome the limitations of the study design and its potential weaknesses. Nonetheless, further research will be needed to replicate our findings.

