After enrolment, participants will be assigned to one of three study groups by randomisation and non-randomisation, depending on the study condition. The groups are as follows: 1) Intervention-initiators (participants who will engage in a supervised exercise programme complemented with a HAPA-based intervention, *n* = 100); 2) control-sedentary (non-active women who will maintain their sedentary lifestyle and will not receive any intervention for promoting behavioural change, *n* = 100) and 3) control-active (women with a regular and sustained exercise habit, *n* = 100).

The sample size has been calculated to include 80 participants per group, considering an *alpha* error of 0.05 and a *beta* error of 0.2, for independent groups and continuous variables, i.e. mean comparisons, with estimated mean values based on previously published studies [64, 65, 68], to ensure sufficient statistical power to detect a moderate treatment effect in a clinical study (Clincalc®). To account for potential dropouts, we anticipate a 20% dropout rate, increasing the sample size up to 100 participants per group. 

Figure 1 shows a flow chart of the study participants, including the selection process.

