### Intervention

A three-component intervention will be offered, which includes:

A multicomponent, supervised exercise programme with a 3-month (12 weeks) minimum duration will be offered to the intervention group. The exercise programme will consist of three 1-h weekly sessions on alternate days. Participants will be able to choose from several schedules available in both the morning and afternoon periods. The programme will be designed and implemented by experts in Exercise and Sport Sciences and Sport and Exercise Medicine, following international recommendations for exercise in middle-aged women [96, 97]. The programme will include training for aerobic cardiorespiratory fitness, muscle resistance, as well as other fitness functions including flexibility, coordination and balance. Hence, it will meet the required conditions in terms of activity type, duration, frequency and intensity parameters and principles and methodology of training for a healthy, safe, successful and enjoyable practice for adult women, thus being suited to their characteristics and needs for maximising benefits while minimising risks. The programme will be implemented in supervised group classes conducted in a gym facility (e.g., in the university campus). To assess adherence to the programme, objective tracking measures will be utilised, including attendance monitoring. All these features are designed to optimise participation as well as outcomes. Additionally, a health insurance policy will be put in place to cover any potential risks and provide necessary medical assistance if required.A simultaneous intervention focusing on self-management of behavioural change, based on the tenets of the HAPA model, will be offered throughout the duration of the exercise programme. This intervention has been designed based on previous HAPA-based interventions [98–103]. To summarise, the intervention will provide information on the benefits of an active lifestyle and exercise, specifically for postmenopausal women, addressing risk perceptions and outcome expectations while facilitating the creation of an intention (Session 1). The participants will be also educated on the key factors for adopting and maintaining an active behaviour, such as identifying barriers and facilitators, basic self-monitoring and self-management skills for action regulation (e.g., self-monitoring, self-reinforcement, setting a daily time schedule, emotional regulation, seeking social support and reinforcement from significant others); these elements contribute to improving motivational action self-efficacy (Session 2). The subsequent 3 to 5 sessions will focus on motivational determinants of exercise initiation, including goal setting (behavioural intention), action planning and pre-actional/task self-efficacy to improve motivation and action initiation. Sessions 6 to 9 will address volitional determinants of maintaining adherence, covering self-regulatory skills including action and maintenance plans for autonomous exercise, maintenance and coping self-efficacy and relapse management (i.e., risk identification, functional responses and coping skills training). A final session is devoted to summarising the personal progress of the participants with this intervention. The aim of this intervention is to ensure that women not only adhere to the supervised exercise programme offered within the study, but mainly to promote long-term, self-managed adherence to the newly established lifestyle beyond the completion of the supervised exercise programme. To achieve this, the adherence promotion intervention will be delivered during the entire implementation of the exercise programme, divided into two phases according to the process of behavioural change. During the first phase of the programme, the focus will be on addressing issues pertaining to initiation and short-term maintenance. Researchers and implementers will play a central role in providing external regulation and support as a strategy to facilitate adherence. During the second phase of the programme, the emphasis will shift toward long-term maintenance. Building on the knowledge and skills acquired by the participants, the intervention will promote the transition to self-regulation and the development of intrinsic motivation based on enjoyment and personal growth.

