The impact of menopause-related changes on women's quality of life is strongly linked to personal and sociocultural characteristics, which significantly determine how each woman experiences the perimenopausal transition and the postmenopausal stage. A growing body of evidence shows the influence of various psychosocial factors on women's health during and after menopause, including their perceptions, beliefs, attitudes and lifestyle habits [114, 115]. These factors can in turn influence women’s engagement in health promotion and disease management programmes, the development of support networks, the seeking of professional help and the choice and adherence to therapies such as hormone therapy and other interventions, including lifestyle changes [27]. Therefore, psychosocial factors are important precursors of good health among women in midlife. For this reason, it has been suggested that this life stage may have a positive — rather than negative — impact on women [116]. While the link between psychosocial factors and women’s personal experiences of menopausal symptoms and health-related decision-making has been extensively studied, it remains unclear as to how these factors interact with biomedical variables for influencing the choice of intervention strategies that women use to manage both menopause symptoms and their effects in the short and long term.

All the above demonstrates the importance of implementing exercise programmes for postmenopausal women. It is also crucial to identify and manage the psychosocial and biomedical factors that determine the initiation and adherence to an active lifestyle, beyond the benefits for a woman’s health, well-being and quality of life. Particularly with respect to the determinants of exercise behaviour in middle-aged women, there is limited literature that considers the experiences, needs, resources and opportunities of women in the postmenopausal period. The latter is especially important if one considers the low adherence to the recommended guidelines [10] and the dropout rates (i.e., from partial or temporary abandonment to total and permanent disengagement) among those who have participated in an exercise programme, so that up to half of these women fail to adopt the new habit, particularly as they age or face health conditions [117]. Moreover, gender inequalities should guide practical and policy-oriented efforts to eradicate the differences among women and men in terms of health and lifestyle [107].

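### The claimed sample-size margin is only the dropout allowance, and the stated 80% power holds only if women taught in the same exercise classes respond independently

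*Protocol article*

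**What the plan says.** The sample size is set out in Participants and eligibility criteria: "The sample size has been calculated to include 80 participants per group", with an alpha "error of 0.05 and a *beta* error of 0.2", "for independent groups and continuous variables, i.e. mean comparisons". The purpose given is "to ensure sufficient statistical power to detect a moderate treatment effect in a clinical study"; no mean, SD or standardised difference is printed. The section continues: "we anticipate a 20% dropout rate, increasing the sample size up to 100 participants per group".

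Strengths and limitations names sample size as an important limitation, then offers as reassurance that "the expected sample size per study subgroup exceeds the calculated sample size".

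Under Intervention, only the intervention group receives the exercise programme: three one-hour sessions a week for at least 12 weeks, on schedules the women choose. "The programme will be implemented in supervised group classes conducted in a gym facility".

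Data management and analyses names t tests, one- or two-way ANOVAs and rank-based equivalents for the group and phase comparisons (H1 to H3). Multilevel clustering appears there only for H4 and H5, to explore predictors and intraindividual profiles. Missing data are handled by pairwise deletion by default, with last observation carried forward as an alternative where feasible.

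**The concern.** There are two linked problems.

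First, the limitations paragraph uses the gap between 100 and 80 as a margin of safety, but that gap is already committed to expected dropout. A reader who takes the paragraph at face value will think the trial has power to spare when its own figures leave none.

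Second, the 80 is an independence-based number and the tests named for H1 to H3 are independence-based tests. Women in the same exercise class share sessions and peers for three months, and they sort themselves by chosen schedule. The primary outcomes are exercise behaviour and social-cognitive constructs, which shared classes could plausibly influence. Any positive within-class correlation makes the information in the intervention arm less than its head count suggests. Comparisons of that arm with the controls after the intervention (H3), and changes within it (H1), would then have standard errors that are too small, too many false positives and less power than stated. The baseline comparison (H2) precedes the classes and is unaffected.

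**Working it through.** **Inputs from the article.** 80 per group, alpha 0.05, power 0.80, dropout 20%, 100 enrolled per group, 1:1 randomisation of the inactive women. Sidedness is not stated; two-sided is assumed.

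**Reproducing the enrolment figure.** 80 / (1 − 0.20) = 100, exactly. Reversed, 100 × (1 − 0.20) = 80. Margin over the calculated size: 80 − 80 = 0.

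**Implied effect.** A two-sided two-sample t test with 80 per group has 80% power at 0.446 SD. This is back-solved, because the article says only that the effect is moderate.

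**Adding class clustering in the intervention arm only.** For class size m and intraclass correlation ICC:

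- Design effect: DE = 1 + (m − 1) × ICC
- Standard error of the difference, in SD units: SE = √[(DE + 1)/80]; without clustering it is √(2/80) = 0.158
- Power at a true 5% level: Φ(0.446/SE − 1.96)
- Type I error of a test that ignores classes: 2 × [1 − Φ(1.96 × √(2/(DE + 1)))]

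The article gives neither m nor ICC, so every row below rests on assumed values.

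| m | ICC | DE | SE | Power | Type I error |
|---|---|---|---|---|---|
| any | 0 | 1.00 | 0.158 | 80% | 5.0% |
| 10 | 0.01 | 1.09 | 0.162 | 79% | 5.5% |
| 20 | 0.01 | 1.19 | 0.165 | 77% | 6.1% |
| 10 | 0.03 | 1.27 | 0.168 | 75% | 6.6% |
| 20 | 0.10 | 2.90 | 0.221 | 52% | 16% |

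The last row worked through: DE = 1 + 19 × 0.10 = 2.90; SE = √(3.90/80) = 0.221; 0.446/0.221 − 1.96 = 0.06, so power is about 52%.

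**Detectable effect with small-sample degrees of freedom.** The table uses normal quantiles. An analysis with a class random effect must also pay for the small number of classes, k = 80/m. The Satterthwaite degrees of freedom are (DE + 1)² / [DE²/(k − 1) + 1/79], and the effect detectable with 80% power is about (t₀.₉₇₅ + t₀.₈₀) × SE.

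- m = 10, ICC 0.03, k = 8: df = 2.27² / (1.27²/7 + 1/79) ≈ 21.2; (2.078 + 0.859) × 0.168 ≈ 0.49 SD.
- m = 20, ICC 0.10, k = 4: df = 3.90² / (2.90²/3 + 1/79) ≈ 5.4; (2.514 + 0.913) × 0.221 ≈ 0.76 SD.

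The unclustered 95% half-width is 1.975 × 0.158 = 0.312 SD. In the two cases it becomes 2.078 × 0.168 ≈ 0.350 (12% wider) and 2.514 × 0.221 ≈ 0.555 (78% wider).

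**The case against.** **The sentence is literally true.** It refers back to the sample-size section, where 100 does exceed 80. Last observation carried forward may also keep some women in some analyses, and if fewer than 20% are lost a real margin appears: 100 analysed per group would give 88% power at 0.446 SD. All of this stands. But the sentence is offered as reassurance about adequacy, the default is pairwise deletion, and at the dropout rate the article itself expects nothing is left over.

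**The clustering harm is conditional.** This also stands. A reader might infer that standard errors are certainly too small and power materially overstated. The documents do not show that: with no ICC, class size or number of classes, the loss may be as little as one to three points of power. The 52% and 16% figures are one corner of an assumed grid. Nor should the design effect be applied to both arms, since exercise classes exist in one arm only.

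**Women may move between classes.** They choose among several schedules and the article does not say they stay in one. The simple nested formula is then an approximation, which the fix has to allow for.

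**The effect might be 0.50 SD.** With independent women, 80 per group would then give 88% power. But the article states a beta of 0.2 at 80 per group, so it claims no such slack.

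**An article leaves modelling detail to the analysis plan.** This is fair for the exact model, and the tests are listed as examples. But the article itself prints the independence-based calculation and the family of tests.

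**A tempting stronger reading.** The Discussion says of women in exercise programmes that "up to half of these women fail to adopt the new habit". A reader might set this against the 20% allowance and conclude that only 50 per group will be analysed. The documents do not support that. The remark concerns abandoning exercise, not missing assessments, and the Intervention section says non-adherent women stay in the study and the analyses.

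**Conclusion.** The point holds on both counts, in a limited form.

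That the claimed margin is the dropout allowance counted a second time is arithmetic on the article's own figures and needs no outside assumption beyond its own 20%. It calls for a correction of wording.

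That the stated 80% power and the H1 and H3 tests rest on independence, while the intervention arm is taught in classes, is also plain from the text. The direction of the consequence requires only an ICC above zero. Its size cannot be determined from the documents. With 80 analysed per group, 0.446 SD and assumed classes of 10 to 20, it runs from slight at ICC 0.01 to serious at ICC 0.10 with classes of 20. This merits correction but does not call the design into question.

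**What to change.** 1. In Strengths and limitations, delete the sentence or reword it to say that 100 enrolled per group is expected to leave the calculated 80 for analysis.
2. In the sample-size paragraph, state that 80 analysed per group gives 80% power for about 0.45 SD only without class clustering. Add the detectable effect under declared class-size and ICC assumptions, using the same small-sample degrees of freedom as the analysis: about 0.49 SD at classes of 10 and ICC 0.03, up to about 0.76 SD at classes of 20 and ICC 0.10.
3. Record each woman's main exercise class. Attendance is already monitored, but the article does not say that class identity is kept.
4. For post-intervention and follow-up comparisons involving the intervention arm, fit a partially nested model: a class random effect in that arm only, with small-sample degrees of freedom, using the main class attended where women move between schedules.

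No extra participants are needed. The cost is one more recorded variable, one more model term and wider intervals: about 12% wider at classes of 10 and ICC 0.03, and much more (about 78% at classes of 20 and ICC 0.10) if classes are few and the correlation is high. Forming more, smaller classes would limit that cost if timetabling allows.

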## Conclusions

In conclusion, the findings of the AHAWOMEN project will provide valuable insights for designing and implementing effective theory-grounded and evidence-based interventions. The midlife stage appears to be a crucial period for interventions aimed at promoting exercise and an active lifestyle, since the ageing population becomes less active — particularly women —, the ageing processes become more evident and health threats and chronic diseases begin to appear. Midlife is thus viewed by many as an opportune time to initiate a change in lifestyle. Embracing an active lifestyle after the menopause can have long-lasting benefits, helping women to remain active for years to come while managing the above-mentioned phenomena. All this stresses the importance of promoting exercise programmes specifically tailored to middle-aged women. Since both the initiation and maintenance of an active lifestyle pose significant challenges, it is essential to manage the psychosocial and biomedical factors that determine short- and long-term adherence. To optimise the benefits of exercise for women’s health, well-being and quality of life, it is crucial to consider the needs, opportunities, resources, experiences and circumstances of women in midlife. The AHAWOMEN project, through multidisciplinary alliances and conceptual and empirical contributions transferable to healthcare and social justice, will provide solutions to the main current societal and public health challenges.

The authors plan to disseminate the findings of this study through publications in peer-reviewed journals and by presenting the work at scientific and professional conferences.

## Data Availability

The datasets used and/or analysed during the current study are available from the corresponding author on reasonable request. There will be no personal identification of participants in the data set.
